## Abstract

**Background:**

Knee osteoarthritis (OA) is a common and disabling condition. Abnormalities in knee loading play an important role in disease pathogenesis, yet there are few non-surgical treatments for knee OA capable of reducing knee load. This two-arm randomised controlled trial is investigating the efficacy of specially-designed unloading shoes for the treatment of symptoms in people with knee OA.

**Methods/Design:**

164 people with symptomatic medial tibiofemoral joint OA will be recruited from the community and randomly allocated to receive either unloading shoes or control shoes. Unloading shoes have a specially-designed triple-density midsole where the medial side is softer than normal and the lateral side harder as well as a lateral wedge between the sole and sock-liner. Control shoes are standard athletic shoes and do not contain these features. Participants will be blinded to shoe allocation and will be instructed to wear the shoes as much as possible every day for 6 months, for a minimum of 4 hours per day. The primary outcomes are knee pain (numerical rating scale) and self-reported physical function (Western Ontario and McMaster Universities Osteoarthritis Index) measured at baseline and 6 months. Secondary outcomes include additional measures of knee pain, knee stiffness, participant global ratings of change in symptoms, quality-of-life and physical activity.

**Conclusions:**

The findings from this study will help determine whether specially-designed unloading shoes are efficacious in the management of knee OA.

**Trial registration:**

Australian New Zealand Clinical Trials Registry reference: ACTRN12613000851763.

## Background

Osteoarthritis (OA) is a leading cause of musculoskeletal pain and disability, particularly amongst older adults. In 2007, 20-25% of Australians over 55 years had OA [1]. This will further increase in coming years due to population ageing and rising obesity rates. Knee OA results in significant knee pain and physical dysfunction that typically worsen over time [2,3]. There is no cure, thus interventions that alleviate symptoms and prevent clinical decline over the long-term are required.

Knee OA results from increased joint loading acting within the context of systemic and/or local susceptibility [4]. As *in vivo* measurement of joint loads is not feasible, three-dimensional gait analysis is used to infer dynamic load. During walking, high loads are applied to the knee. An external knee adduction moment (KAM) is generated because the ground reaction force vector passes medially to the knee during stance [5]. This moment (or torque) tends to force the knee outwards, compressing the medial joint compartment and stretching lateral joint structures. In fact, abnormal medial load resulting from the KAM probably explains why knee OA occurs mostly in the medial tibiofemoral joint [6].

The KAM (measured as peak and/or the related KAM impulse) is a valid surrogate for medial knee load. The KAM is higher in people with medial knee OA [7-9] compared to controls, and it strongly predicts OA radiographic severity [10]. The KAM has also been shown to predict treatment outcome in patients undergoing high tibial osteotomy [11]. A higher KAM is associated with development of knee pain in older people [12], as well as with increased pain severity and physical dysfunction in people with knee OA [13,14]. Relationships between both the peak KAM and the KAM impulse and presence of medial knee bone marrow lesions have been demonstrated [15], which are an important source of pain in knee OA [16]. The KAM is one of only a few factors known to predict OA disease progression. A 1-unit increase in the peak KAM is associated with up to a 6.5-fold increase in the risk of disease progression over 6 years [13]. Thus, given its relationship to symptoms and clinical outcome in knee OA, there is increasing interest in mechanical interventions directed at lowering the peak KAM.

Clinical guidelines emphasise that appropriate footwear should be worn by people with knee OA [17]. This recommendation is based on expert opinion given the scant research evidence available. Wearing shoes significantly *increases* medial knee load compared to barefoot walking [18,19]. Recent research, by ourselves and others, has developed specialised shoes for people with knee OA with variable-stiffness soles that are denser laterally compared to medially in order to reduce the KAM [20-22]. Thus, when weightbearing, the greater medial compressibility effectively creates a laterally angled shoe that reduces the frontal plane lever arm of the ground reaction force at the knee joint centre, reducing the KAM [23,24]. These types of modified shoes can immediately reduce the KAM by 3.5-7.9% in people with medial knee OA [20,25]. In a single case study involving a patient with an instrumented knee replacement, variable-stiffness shoes reduced the peak KAM by 13.3% and medial joint contact force by 12.3% [22]. Furthermore, change in KAM correlated with change in contact force, validating the load-modifying effects of unloading shoes for knee OA.

Relative to their biomechanical effects, there is very little known about whether unloading shoes can reduce the pain and physical dysfunction associated with knee OA. There is only one randomized controlled trial (RCT) evaluating clinical benefits of variable-stiffness unloading shoes for knee OA [25,26]. The unloading shoes resulted in significant within-group pain reductions after 6 and 12 months of use, however the change in symptoms was not significantly different to that seen in the group wearing control shoes. This may be because of the relatively small sample size utilized (n = 79) and/or the large drop-out rate in the control group (n = 13 out of 39, 33%) by 6 months. Further RCTs are required before the efficacy of unloading shoes for managing the symptoms of OA can be known.

The primary aim of this study is to evaluate the efficacy of specialized unloading shoes on OA-associated symptoms in people with knee OA. We hypothesise that unloading shoes will reduce pain and improve self-reported physical function after 6 months when compared to control shoes.

## Methods/design

### Trial design

The SHARK (SHoes for ARthritis of the Knee) trial is a two-arm participant- and assessor-blinded parallel-group RCT comparing unloading shoes to control (non-unloading) shoes (Figure 1). The protocol conforms to CONSORT guidelines for reporting of non-pharmacological interventions [27]. The primary end-point for analysis of outcomes is after 6 months of treatment.

**Figure 1 F1:**
[figure not shown]
Flow diagram of study protocol.

### Participants

We will recruit 164 participants with medial tibiofemoral OA from the community via advertisements, media campaigns, social media (eg Facebook) and from our research volunteer database. Knee OA will be classified according to the American College of Rheumatology criteria [28]. Participants will be included if they i) are aged ≥50 years ii) report knee pain on most days of the past month; iii) report a minimum average pain score of 4 on an 11-point numerical rating scale (NRS, with terminal descriptors of ‘no pain’ and ‘worst pain possible’) in the past week; iv) demonstrate definite x-ray evidence of OA (Kellgren & Lawrence [29] Grade ≥ 2) and; v) demonstrate definite medial tibiofemoral compartment OA on x-ray (defined as ≥ grade 1 medial osteophytes AND ≥ grade 1 medial joint space narrowing that is greater than lateral joint space narrowing, using a standard atlas [30]).

Participants will be excluded if they i) have more severe lateral tibiofemoral compartment osteophytes relative to medial; ii) have undergone intra-articular corticosteroid injection or knee surgery to either knee within past 3 months; iii) have a systemic arthritic condition; iv) have had a knee joint replacement or high tibial osteotomy in the past, or plan to undergo surgery to either knee in next 6 months; v) have any other muscular, joint or neurological condition affecting lower limb function; vi) current or previous (within 6 months) use of shoe inserts, knee or ankle braces or customized shoes prescribed by a health professional; vii) are unable to walk unaided; viii) have a body mass index ≥ 36 kg/m^2^ (due to difficulties in three-dimensional gait analysis) or; ix) have ankle/foot pathology/pain on either side.

### Procedure

Figure 1 outlines the trial phases. Volunteers will undergo initial screening via an online survey. Further screening will then occur via questioning over the telephone. Potentially eligible volunteers will then undergo x-ray screening to confirm eligibility. Baseline and 6-month assessments (primary time-point) will be carried out at the Department of Physiotherapy, the University of Melbourne. Additionally, participants will complete monthly log-books at home (mailed back to the researchers), will monitor daily physical activity levels for one week during months 2 and 5, and will complete primary outcome measures at home (mailed back to researchers) at 3 months (secondary time-point). Ethical approval has been obtained from the University of Melbourne Human Research Ethics Committee (HREC No. 1239045). All participants will provide written informed consent. For participants with bilaterally eligible knees, only the most symptomatic knee (as identified by the participant) will be evaluated, although the allocated shoes will be worn bilaterally.

### Randomisation and allocation concealment

Eligible participants will be randomised following baseline data collection of primary and secondary outcome measures to receive either unloading shoes or control shoes. Randomisation will be by random permuted blocks of size from 6 to 12 and stratified by radiographic disease severity (Kellgren and Lawrence grades 2, 3 and 4 [29]). The randomisation schedule will be prepared by the study biostatistician. To conceal randomisation, consecutively numbered, sealed, opaque envelopes will be used and kept in a locked location.

Participants will be blinded to which treatment group they are allocated and allocated shoes will have no identifying model or brand. The unloading shoes are visually similar to the control shoes to maintain participant blinding. Participants will be asked to indicate which group they believe they are in order to measure the success of blinding. As all primary and secondary outcomes are participant-reported questionnaires, and participants will be blinded to group allocation, the assessor is also blinded in this study. An investigator, who will also be blinded to group allocation, will oversee administration of all primary and secondary outcome measures. Additional biomechanical and gait analysis measures (that will not be used to determine treatment efficacy but will be used in subsequent analyses to evaluate predictors of treatment response) will be conducted by another investigator who is not blinded to group allocation by necessity due to the nature of the biomechanical testing procedures.

### Interventions

Participants will be provided with a pair of shoes (allocation according to the randomisation schedule) appropriately sized to their feet. Participants will be instructed to wear their allocated shoes as much as possible every day for 6 months, and to avoid wearing their usual shoes as much as possible. At a minimum, participants will be asked to wear the shoes for at least 4 hours every day. Participants will be advised to initially wear the shoes for one hour, and thereafter increase by one hour each day until wearing the shoes for all waking hours.

### Unloading shoes

Black recreational walking shoes (Gel-Melbourne OA, Asics) that have been designed to unload the medial compartment of the knee [20] will be used. These shoes have a specially-designed triple-density sole of compression moulded ethylene vinyl acetate, where the lateral midsole is stiffer than the medial. They also contain a thin, full-length, half-width laterally-biased wedge (approximately 5 degrees angulation) attached to the underside of the sock-liner.

#### Control shoes

Black neutral recreational walking shoes (Gel-Odyssey, Asics) that are similar in appearance to the unloading shoes, but do not contain the the stiffer lateral midsole nor a lateral wedge insert will be used.

### Treatment adherence

Treatment adherence will be self-reported in a log-book. For the fourth week of each month (to reduce the burden on participants), participants will record how many hours each day they wear their allocated shoes, for 7 consecutive days. They will also rate their perceived overall level of compliance over the past month with the instruction to wear their allocated shoes for a minimum of 4 hours per day on an 11-point NRS (with terminal descriptors of ‘not at all’ and ‘completely as instructed’). Log-books will be posted back to investigators on a monthly basis. Participants will also rate their overall level of compliance over the 6-month treatment period using an identical NRS at the 6-month assessment. At this time, participants will also be asked to estimate, on average, how many hours per day they wore their allocated shoes for the 6-month treatment period.

Treatment adherence (over a one-week interval) will further be monitored at two time-points (2 months and 5 months) by the use of pedometers. For 7 consecutive days, participants will be asked to attach and wear a shoe pedometer (Oregon Scientific PE903, Oregon, USA) to one of their allocated trial shoes. Participants will also be asked to wear a second pedometer at their waist during waking hours (Omron HJ720ITC Pedometer, Omron Healthcare, Illinois, USA) over the same period in order to capture daily step counts irrespective of footwear worn. For each participant at each time-point, we will calculate the proportion of daily steps taken whilst wearing their allocated shoes. Participants will be telephoned prior to the week of pedometer data collection to facilitate adherence with pedometers.

### Adverse effects of treatment, shoe comfort and co-interventions

Adverse events will be defined as any problem believed by participants to be caused by the allocated shoes that lasted for two days or more and/or caused the participant to take medications or see a health professional. Participants will record any adverse effects of treatment in the monthly log-books. At the 6-month assessment, adverse effects will also be ascertained by open-ended questioning by the blinded assessor.

Monthly log-books will also be used to record participant ratings of shoe comfort. Participants will rate their overall level of shoe comfort experienced over the past month via an 11-point NRS (with terminal descriptors of ‘extremely uncomfortable’ and ‘extremely comfortable’). Participants will also rate their overall level of shoe comfort over the 6-month treatment period using an identical NRS at the 6-month assessment.

Use of co-interventions (medications for knee pain and any other treatments for knee OA) will also be recorded in the monthly log-books. At the 6-month assessment, use of co-interventions will also be ascertained by open-ended questioning by the blinded assessor.

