### Sample size calculations

The trial is powered to detect clinically important changes in the primary outcomes of knee pain on walking (NRS) and change in physical function (WOMAC). The minimum clinically important difference to be detected in OA trials is a change in pain of 1.8 units (out of 10) [41] and change in function of six units (out of 68) [42]. Our calculations are based on SD’s from our unpublished pilot data of the effects of unloading shoes, and on control group data from our previous RCT of lateral wedged insoles [43]. We assume a between-subject SD of 2.5 for pain and 10.5 units for WOMAC physical function, and a baseline to 12-month correlation in scores of 0.29 for pain and 0.51 for physical function. These assumptions, together with an analysis of covariance adjusted for baseline scores, require a sample size of 41 participants per group to achieve 90% power to detect the minimum clinically important difference in pain. A similar analysis for function scores requires 65 participants per group. Allowing for a 20% attrition rate, we will recruit 82 participants per arm, or 164 participants in total.

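### Adverse events count only if the participant blames the shoes, so harms not linked to the shoes are neither counted nor actively sought (minor; inexpensive to correct)

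*Protocol article*

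**What the plan says.** All of the harm-related text is in the protocol article's section on adverse effects, shoe comfort and co-interventions.

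- **Definition, first condition:** "Adverse events will be defined as any problem believed by participants to be caused by the allocated shoes".
- **Definition, second condition:** the problem must also be one "that lasted for two days or more and/or caused the participant to take medications or see a health professional".
- **First collection route:** "Participants will record any adverse effects of treatment in the monthly log-books".
- **Second collection route, at 6 months:** "adverse effects will also be ascertained by open-ended questioning by the blinded assessor".
- **Co-interventions:** these are also logged, but their scope is the study condition: "Use of co-interventions (medications for knee pain and any other treatments for knee OA").

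The article describes no collection of health problems regardless of cause, no list of events to ask about, and no separate step in which relation to the shoes is judged. The statistical analyses section does not mention adverse events.

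**The concern.** The participant's causal opinion is part of the definition, so it decides whether an event exists for the trial. The unloading shoe is meant to change lower-limb mechanics: it has a stiffer lateral midsole and a lateral wedge of about 5 degrees, and it is to be worn for most of the day for 6 months by people aged 50 or over. If it does harm, the harm could appear away from the foot, where a lay person may not suspect a shoe.

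In a randomised trial with blinded participants nobody has to judge the cause of a single event, because an excess in one arm is itself the evidence. Filtering on belief gives up that advantage. At stake is the harms summary that will accompany the efficacy result. The Discussion says the findings should help clinicians and patients choose footwear.

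**Working it through.** **Step 1: does another route close the gap?**

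| Source in the protocol article | Would it capture a fall, or pain at another joint, that the participant does not link to the shoes? |
|---|---|
| Monthly log-book | Not sought: it is described as recording adverse effects of the treatment |
| 6-month open-ended questioning | Not sought: it also concerns adverse effects. Such a problem may surface by chance but would not meet the definition |
| Co-intervention record | No: limited to knee pain medication and knee OA treatment |
| NRS, WOMAC, ICOAP | No: these are knee pain, stiffness and function measures, and only one knee per person is evaluated |
| AQoL-6D, PASE | Partly: they do not depend on belief and are taken in both arms, but they do not itemise falls or pain sites |

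No stated route seeks these events irrespective of cause.

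**Step 2: what does the filter do to a comparison by arm?** The plan gives no adverse event rate, harm margin or safety power, so there is no figure to reproduce. Every rate and share below is an assumption. Only the 82 per arm comes from the plan (Sample size calculations), and drop-out is ignored.

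Let p1 and p0 be the true proportions with a qualifying problem (unloading, control), and a1 and a0 the shares that participants attribute to the shoes. The recorded proportions are q1 = a1·p1 and q0 = a0·p0.

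- Recorded difference = a1·p1 − a0·p0. If a1 = a0 = a, this is a·(p1 − p0).
- Recorded risk ratio = (a1/a0)·(p1/p0). If a1 = a0, it equals the true ratio.

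Simple case, with p1 = 15%, p0 = 5% and a = 1/3: q1 = 5.0% and q0 = 1.7%. The difference falls from 10 to 3.3 points. The risk ratio is 15/5 = 3 before and 5.0/1.67 = 3 after.

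**Step 3: evidential strength at 82 per arm.** Power is for a two-sided 5% test of two proportions: Φ[(d − 1.96·se0)/se1], where d is the absolute recorded difference, se0 uses the pooled proportion and se1 the separate proportions. For 30% against 15%: pooled 22.5%, se0 = √(0.225 × 0.775 × 2/82) = 0.0652, se1 = 0.0642, so Φ[(0.15 − 0.1278)/0.0642] = Φ(0.346), about 64%.

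| True rates | Attributed (unloading / control) | Recorded rates | Difference | Risk ratio | Power |
|---|---|---|---|---|---|
| 30% v 15% | 100% / 100% | 30% v 15% | 15 points | 2 | about 64% |
| 30% v 15% | 50% / 50% | 15% v 7.5% | 7.5 points | 2 | about 33% |
| 30% v 15% | 30% / 30% | 9% v 4.5% | 4.5 points | 2 | about 21% |
| 30% v 15% | 30% / 50% | 9% v 7.5% | 1.5 points | 1.2 | about 5% |
| 20% v 20% | 60% / 30% | 12% v 6% | 6 points | 2 | not applicable (no true difference) |

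The preserved risk ratio is also estimated less precisely. The standard error of its logarithm, √[(1 − q1)/(82·q1) + (1 − q0)/(82·q0)], rises from 0.31 (first row) to 0.47 (second) and 0.62 (third).

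The first three rows show the effect of equal under-attribution. The last two show that unequal attribution can nearly remove a true excess or create one where none exists. Nothing in the documents says which row is closest to the truth.

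**The case against.** The strongest reply is that the rule is explicit, internally consistent and limited in its consequences. Several parts of it stand.

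- A reader might infer that unattributed harms are never recorded. The text does not go that far. It defines what counts, and open-ended questioning may bring up something the participant had not written down. What the text supports is not counted and not sought.
- A reader might infer that falls or problems at other joints are excluded as a class. They are not: a problem at any site counts once it is attributed and meets the second condition.
- A reader might infer that the comparison is biased towards one arm. That is not shown. Participants are blinded, the shoes look alike and carry no branding, and the plan checks this: "Participants will be asked to indicate which group they believe they are in order to measure the success of blinding". Comfort, one route by which suspicion could differ, is rated monthly and at 6 months and can be examined. Unequal attribution remains only a possibility, for instance if the wedge is felt.
- A reader might infer that a planned safety test is invalidated. The article describes none, adverse events are not among the listed outcomes, and the primary aim is efficacy. The effect is on whatever summary by arm is reported.
- With equal attribution the relative comparison survives, and the generic quality-of-life and activity scales give some information that does not depend on belief.

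It can also be said that a condensed article may omit all-cause reporting of serious events that a fuller protocol contains. That may be so, but it would not alter the definition stated here, and no analysis plan can recover events that were never asked about.

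**Conclusion.** The point holds, as a minor one. As written, the definition leaves out harms that participants do not connect with the shoes, and no other described route looks for them. If attribution is incomplete, under-counting follows directly. The absolute excess shrinks in proportion to the share attributed (10 to 3.3 points, or 15 to 7.5 or 4.5 points, in the assumed examples). The evidence weakens with it (power about 64% to 33% or 21% at 82 per arm), while the risk ratio is unchanged if attribution is equal. Distortion between arms requires unequal attribution, for which the documents give no evidence.

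This rests on two assumptions: that the log-book and the 6-month question follow the article's definition, since the forms are not shown, and that some shoe-related harms go unrecognised by participants. The primary and secondary efficacy analyses are unaffected.

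**What to change.** Define an adverse event as any new or worsened health problem, including a fall, that meets the present threshold of duration, medication or health-professional contact, whatever the participant thinks caused it. Reword the log-book entry and the 6-month question to match. Ask as a separate item whether the participant thinks the shoes were responsible. Report all events by arm, with attributed events as a subset, so that the current measure is kept.

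The cost is small: new wording on two forms and more unrelated events to code. Recruitment began in August 2013, so some log-books may already have been completed under the existing wording. Those participants must be reported separately by log-book version, which splits harms data that may already be sparse.

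### The adverse-event definition leaves out a short, untreated shoe problem that makes a participant stop or cut back wear, and does not say whether a problem recurring with each wear has lasted two days

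*Protocol article*

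**What the plan says.** The definition is in the protocol article under Adverse effects of treatment, shoe comfort and co-interventions. It has two parts.

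- **Attribution:** "Adverse events will be defined as any problem believed by participants to be caused by the allocated shoes".
- **Threshold:** the problem must also be one that "lasted for two days or more and/or caused the participant to take medications or see a health professional".

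The same section gives two routes of collection: "Participants will record any adverse effects of treatment in the monthly log-books", and "At the 6-month assessment, adverse effects will also be ascertained by open-ended questioning by the blinded assessor". Neither sentence repeats the threshold. Comfort is rated separately: "Participants will rate their overall level of shoe comfort experienced over the past month via an 11-point NRS", and again over the whole period at 6 months.

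Under Treatment adherence, in the fourth week of each month, "participants will record how many hours each day they wear their allocated shoes, for 7 consecutive days". Participants also give monthly and 6-month compliance ratings, and pedometers at months 2 and 5 give the share of steps taken in the trial shoes.

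Under Interventions, the shoes are introduced gradually: "Participants will be advised to initially wear the shoes for one hour, and thereafter increase by one hour each day".

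**The concern.** The threshold recognises three consequences of a problem: duration, medication and a professional consultation. For a shoe there is a fourth, which is to stop wearing it or wear it less. That response often ends the problem, so it can keep the problem below the duration criterion and make medicine or a visit unnecessary. The gradual build-up makes short early problems followed by removal plausible.

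What is at stake is the tolerability comparison. A reader choosing footwear would want to know how many people in each arm gave up or cut back the shoes because of a problem, and the adverse-event count as defined does not contain all of them. Separately, the word *lasted* is not defined for problems that come and go with wear, so two people coding the same log-book entry could score it differently.

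**Working it through.** No arithmetic applies. The check is to apply the stated definition to cases. In each, the participant blames the shoes, so the attribution part is met.

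| Case | Two days or more? | Medication? | Professional seen? | Adverse event? |
|---|---|---|---|---|
| (a) Pain during wear, shoes removed, pain gone the same day, wear stopped or reduced, no recurrence | No | No | No | **No** |
| (b) As (a), but a painkiller is taken or a professional is seen | No | One or both | One or both | Yes |
| (c) Pain clears when the shoes come off but returns with each wear over two or more days, untreated | Not determined by the text | No | No | **Undetermined** |
| (d) Pain persists two days or more after removal | Yes | Either | Either | Yes |

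The criteria are joined by and/or, so any one is enough. That is why (b) and (d) count. Case (a) meets none of the three. Case (c) turns on whether *lasted* means continuously present or present on and off, which the section does not say.

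Next, whether the other data recover case (a):

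1. **Log-book entries and 6-month questioning.** Both ask about adverse effects in general terms, so the problem may be written down or mentioned. If it is, the stated definition still leaves it out of the count.
2. **Comfort rating.** One number per month. As described, it identifies no event, body site or reason for stopping.
3. **Wear hours, compliance ratings and pedometers.** These would show low or no wear but, as described, not why. Timing adds to this. Starting at one hour and adding one hour a day, the four-hour minimum is reached on day 4, whereas hours are first logged in the fourth week. Someone who stops in the first week would appear there as zero hours.

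The information is therefore partly collected, but no described measure combines a problem with its effect on wear.

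**The case against.** The case for leaving the definition alone has several parts.

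- **A duration-or-consequence threshold is a legitimate way to separate events from break-in discomfort**, particularly with a gradual build-up. This stands as a reason to keep the existing criteria. It is weaker for a problem serious enough to end or reduce wear, which is itself a consequence.
- **Much is already collected**, through open log-book entries, open-ended questioning, comfort, hours and pedometers. This stands and lowers the severity. It does not change what the definition counts.
- **A condensed article may leave log-book wording and reasons for withdrawal to the full protocol.** This stands for those items, and their absence is not the point. The definition itself is stated, and the point concerns what it says.
- **Recruitment began in August 2013, so a change would fall mid-trial.** This stands as a real cost.

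A reader might also infer more than the text supports:

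- *That every problem resolving on removal is excluded.* It is not: case (b) counts.
- *That recurrent pain is excluded.* The text is ambiguous on this; it does not exclude it.
- *That the size can be read from the 20% attrition allowance, or from "the large drop-out rate in the control group (n = 13 out of 39, 33%) by 6 months".* The first is a sample-size allowance and not a rate of giving up shoes. The second is drop-out in another trial, with no tolerability reason given. Neither yields a number of missed events here.
- *That the count would favour the worse-tolerated shoe.* One definition applies to both arms and participants are blinded. The shoes differ in midsole and wedge, so equal under-counting is not assured, but nothing in the document shows a difference or its direction.

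**Conclusion.** The point holds in a narrow form. A problem that lasts under two days, is untreated, is blamed on the shoes and leads to stopping or reducing wear is not an adverse event under the stated definition, and the status of a problem recurring with each wear is undefined. The consequence is possible under-counting of tolerability problems in the harms comparison.

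Its size cannot be derived from the document, and no figure is offered. Adverse events are not among the primary or secondary efficacy outcomes, so the efficacy conclusions and the sample size are unaffected. The severity is minor: a cheap improvement to harms reporting.

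The conclusion rests on reading the definition as the rule for what is counted. If all log-book entries were to be reported whatever their duration or consequence, most of the gap would close for problems that participants write down.

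**What to change.** - **Definition:** add a further criterion, that the problem caused the participant to reduce or stop wearing the allocated shoes. Keep the existing criteria.
- **Recurrence:** state that repeated episodes of the same problem count as one event, running from the first episode to the last.
- **Collection:** add a matching item to the monthly log-book and a matching question at the 6-month assessment.
- **Reporting:** give by arm the number who reduced or stopped wear because of a problem, alongside all log-book adverse effects regardless of threshold.

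The cost is a phrase in the definition, a sentence on recurrence, one log-book item, one question and the added lines in the harms table. There are two downsides. More minor events will be recorded. Participants already followed will not have had the new item, so for them the by-arm report must rely on free-text log-book entries and the 6-month questioning, and the report should say so.
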